### Randomisation and masking

Clusters were randomly assigned to one of four intervention arms using a restricted randomisation procedure [28]. Restricted randomisation involves modelling selection using a set of village-level variables to ensure balance across the intervention arms. The variables in the restricted randomisation were selected based on their potential influence on the main study outcomes and their potential influence on participation in the interventions [28]. The village-level variables included in the model were population size, total per capita household expenditure, household dwelling state, household drinking water source, women’s empowerment, maternal caloric intake, maternal micronutrient intake, maternal age, pregnancy status, maternal weight, maternal education, maternal marital status, child age, child sex, child weight, child height, and child and total MDAT score. Household-level data were used to generate village-level aggregates for all variables except for population size which was available at the village level. We developed a programme using Stata 17 [29] to randomly allocate clusters to four different arms stratifying by district. The randomisation was stratified by district to allow for the same approximate number of clusters within each of the intervention arms in each of the two districts. The algorithm then regressed selection into the intervention arm on the village-level variables. The algorithm tested 5000 random allocations and then selected the permutation that minimised the *R*^2^ for the predicted selection. Description of the intervention arms is provided in Table 2.

**Table 2 Tab2:** Description of the four intervention arms

Intervention arm	Care group component	SBC component	Cash transfer component	Number of clusters
Standard of care (SoC)	Yes	No	No	39
Nutrition-sensitive social and behaviour change (SBC)	Yes	Nutrition-sensitive SBC on agriculture, gender, adolescence, and extra ECD	No	39
SBC + low cash	Yes	Nutrition-sensitive SBC on agriculture, gender, adolescence, and extra ECD	~ $17 per month	39
SBC + high cash	Yes	Nutrition-sensitive SBC on agriculture, gender, adolescence, and extra ECD	~ $43 per month	39

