### Statistical analysis

The randomised design allows for the identification of causal impacts of the interventions using comparisons of mean outcomes between the randomised intervention arms at endline. The analysis will follow the intention-to-treat approach, using econometric analysis to control for differences at baseline across intervention arms for all variables of interest. Following Bruhn and McKenzie [36], impact will be assessed using a single difference analysis of covariance (ANCOVA) model with the following form:$${Y}_{i1}={\beta }_{0}+{\beta }_{1}{T}_{i}+{{\beta }_{2}Y}_{i0}+{\varepsilon }_{i}$$where $${Y}_{i0}$$ is the outcome variable at baseline, $${Y}_{i1}$$ is the outcome variable at endline, and $${T}_{i}$$ is a dummy variable for treatment status. The ANCOVA estimator has been shown to provide more efficient estimates of programme impact than difference-in-difference models when auto-correlation of outcomes is low [36]. To account for the cRCT design and the level of clustering of the outcome under analysis, we will employ multi-level regression models [37]. The multi-level models will use both fixed effects with dummy variables for each intervention and random effects at the cluster level (unit of randomisation) to account for clustering and to estimate the standard error in an unbiased manner. Alternative fixed effect models with standard errors clustered at the cluster level will also be considered. Primary analyses will be unadjusted for baseline covariates. In addition, we will report adjusted estimates, controlling for baseline covariates. We will also adjust for the study district to account for any agro-ecological differences that may influence the food security and livelihood interventions. The purpose of the adjustment is to account for imbalances at baseline and to reduce variance. The intent-to-treat analysis strategy will include attempts to follow up all individuals in the study, the development of a main analysis that is valid under a stated plausible assumption on missing data, and sensitivity analysis to explore the effects of departures from the assumption underlying the main analysis. Data management, data cleaning, and statistical analyses will be conducted using Stata, SAS, and R. Results will be reported following the guidelines established in the CONSORT guidance for cRCTs [38].

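### The primary model is stated as unadjusted and does not clearly include the variables that governed allocation; if those are prognostic, its standard errors are too large and its tests conservative

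*Protocol article*

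**What the plan says.** Under Randomisation and masking, "The randomisation was stratified by district", and within that constraint "The algorithm tested 5000 random allocations and then selected the permutation that minimised the" R² from regressing arm on village-level variables. The list begins "The village-level variables included in the model were population size, total per capita household expenditure" and runs to 17 or 18 items, depending on whether the MDAT entry counts as one or two. It includes maternal micronutrient intake and MDAT score, the baseline counterparts of the two primary outcomes. The section says the variables were picked for their possible influence on the main outcomes and on participation.

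Under Statistical analysis, the approach is described as "using econometric analysis to control for differences at baseline across intervention arms for all variables of interest", and "impact will be assessed using a single difference analysis of covariance (ANCOVA) model" whose equation contains the baseline outcome Y_i0. A cluster random effect is added, with the stated aim of an unbiased standard error. The section then says "Primary analyses will be unadjusted for baseline covariates", followed by "In addition, we will report adjusted estimates, controlling for baseline covariates" and "We will also adjust for the study district to account for any agro-ecological differences". The adjustment covariates are not named. District is justified by agro-ecology, not by its role as a stratum, and no sentence assigns it to the primary or the additional model.

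**The concern.** When allocation is chosen to be balanced on a set of variables, chance differences between arms on those variables are smaller than under simple randomisation. An analysis that leaves them out still estimates its standard error from all the between-cluster variation, including the part that the design has largely taken out of the arm comparison. If the variables predict the outcome, the reported standard error exceeds the true one and the test rejects less often than its nominal level. The section's aim of an unbiased standard error is then not met.

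The second difficulty is that the text does not settle what the primary model is. Y_i0 is itself a baseline covariate, so the equation and the word unadjusted do not sit together as written. The primary estimate could contain Y_i0, district, both or neither.

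Power matters here because the protocol's own benchmarks leave little room: a cited effect of 0.34 SD against a minimum detectable effect of 0.31 SD for MPA, and 0.23 SD against 0.26 SD for MDAT.

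**Working it through.** **Inputs from the protocol.** 156 clusters, 4 arms of 39, 2 districts, best of 5000 allocations, 17 or 18 balancing variables (18 used); about 20 pairs per cluster; ICC 0.05 (MPA) and 0.02 (MDAT).

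**Assumptions.** The share of cluster-mean outcome variance explained by the balancing variables is not given, so a range is used. The simulated variables are independent and normal, and the baseline outcome enters as a village mean.

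**The plan's own figures.** The protocol states no standard error or test size, only detectable effects. With MDES = (z_α + z_power)·√[2(1+19·ICC)/(40·20)], two-sided 0.05 and 80% power:
- MPA: 2.802 × √(2×1.95/800) = 2.802 × 0.0698 = 0.196
- MDAT: 2.802 × √(2×1.38/800) = 2.802 × 0.0587 = 0.165

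The stated 0.31 and 0.26 are not reproduced. They imply a multiplier of about 4.43. Alpha and power are not stated, so this does not show them to be wrong, and nothing below depends on them.

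**How far the restriction goes.** In simulation, the mean R² of arm on the 18 variables is 0.116. The best of 5000 averages 0.054. Covariate imbalance falls to about v = 0.46 of its value under simple randomisation (0.36 with 12 variables, 0.53 with 24).

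**Test size and standard error.** 500 allocations × 20 outcome draws × 3 contrasts with standard of care, no true effect, cluster-mean regression (equivalent to a random intercept with equal cluster sizes). Weak, mid and strong mean that the balancing variables plus district explain 17%, 35% and 55% of cluster-mean variance.

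| Model | Size: weak / mid / strong | Reported SE ÷ true SE |
|---|---|---|
| Unadjusted | 0.040 / 0.028 / 0.017 | 1.05 / 1.12 / 1.21 |
| Y_i0 only | 0.043 / 0.035 / 0.027 | 1.035 / 1.08 / 1.135 |
| Y_i0 + district | 0.045 / 0.041 / 0.033 | 1.02 / 1.05 / 1.09 |
| All balancing variables + district | 0.051 / 0.053 / 0.050 | 0.99 / 1.00 / 1.00 |

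With non-prognostic variables, the unadjusted size is 0.051 and there is no distortion.

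**Analytic check.** True variance ÷ reported variance = 1 − ρ²(1 − v), where ρ² is the explained share. At ρ² = 0.4: 1 − 0.4×0.544 = 0.782, so the SE is overstated by 1/√0.782 = 1.13 and size is 2Φ(−1.96×1.13) = 0.027. This lies between the mid and strong rows.

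**Anchoring to the protocol's ICCs.** The between-village share of cluster-mean variance is ICC/[ICC + (1−ICC)/20]:
- MPA: 0.05/(0.05+0.0475) = 0.51
- MDAT: 0.02/(0.02+0.049) = 0.29

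If the balancing variables explain half of that (ρ² = 0.256 and 0.145), the unadjusted SE is overstated by 1/√0.861 = 1.08 and 1/√0.921 = 1.04. Size is about 0.035 for MPA and 0.041 for MDAT.

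**Power.** Take the effect that the full model detects with 80% power. In the mid case, with reported SE 0.1875 and true SE 0.1883 (in SDs of cluster means), this is 1.96×0.1875 + 0.8416×0.1883 = 0.526.
- Unadjusted (reported 0.2266, true 0.2017): Φ[(0.526 − 0.444)/0.2017] = 0.66
- Y_i0 + district (reported 0.2028, true 0.1931): Φ[(0.526 − 0.397)/0.1931] = 0.75

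The same steps give 0.76 and 0.78 in the weak case, and 0.48 and 0.68 in the strong case.

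**The case against.** **The equation may be the primary model.** It contains Y_i0 and is introduced as the way impact will be assessed, and the district sentence may apply throughout. Unadjusted would then mean only that nothing further is added. This is a natural reading, and on it the conflict is one of wording. It stands as a reason not to call the plan self-contradictory in substance. It does not remove the point: with Y_i0 and district in the model, size is still 0.045 to 0.033.

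**The larger effects need strong covariates.** The strong case (55%) exceeds all the between-village variance for both outcomes, and the mid case (35%) exceeds it for MDAT. Reaching those values requires baseline data on the same people to explain person-level variation too. That is possible, but children in utero at baseline have no baseline MDAT. A reader might infer that the nominal 5% test really runs at about 2%. The documents do not support one such figure. It needs a model with neither Y_i0 nor district and a high explained share that they do not state.

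**Nothing is invalid.** Correct: the error is conservative. A reader might also infer that the gain from restricted randomisation is thrown away. It is not, because the better balance is kept in the point estimate and only the reported standard error fails to show it. Part of the apparent benefit of adjustment is that correction. Between the unadjusted and full models the reported SE falls by 6%, 17% and 31%, but the true SE by only 1% (0.2157 to 0.2137), 7% (0.2017 to 0.1883) and 16% (0.1870 to 0.1564).

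**Free choice of result after the fact.** A reader might infer this too. The text does rank unadjusted as primary and adjusted as additional, and it blinds the impact analysts to assignment. What stays open is whether Y_i0 and district are in the primary model. The full covariate list may properly sit in an analysis plan that is not shown, but a stated primary model that omits the design variables is a choice made here.

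**Conclusion.** The concern holds as a matter of precision and clarity, not validity. The protocol balances allocation on variables that it presumes prognostic, labels the primary analysis unadjusted, and leaves the place of Y_i0 and district unsaid. If the variables are prognostic, the primary standard error is overstated: by about 5% to 21% with no adjustment and 2% to 9% with Y_i0 and district, over explained shares of 17% to 55%. At the protocol's ICCs, with half the between-village variance explained, the unadjusted figures are about 8% (MPA) and 4% (MDAT). If they are not prognostic, there is no distortion. The direction is certain given prognostic variables. The magnitude is not, because the explained share is an assumption. This should be fixed, but it does not threaten the validity of the trial's conclusions.

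**What to change.** Replace "Primary analyses will be unadjusted for baseline covariates" with one stated primary model for each primary outcome:
- arm dummies and district, the latter named as the stratification factor;
- baseline outcome Y_i0 where it exists, with an indicator for children in utero at baseline;
- the village-level balancing variables, or a prognostic subset fixed in advance;
- a random effect for cluster.

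Report the unadjusted contrast as a sensitivity analysis. A randomisation test that re-runs the stratified best-of-5000 algorithm is an optional addition.

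The cost is wording, plus up to about 19 cluster-level degrees of freedom out of 156 (18 variables and district), using baseline data already used for the allocation. If the variables prove non-prognostic, the full model's true SE was about 3% larger in simulation (0.2330 against 0.2272). A short pre-specified subset limits that loss. The change should be made before endline data are analysed.

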## Discussion

ECD programmes are considered among the most cost-effective investments in human capital [9], resulting in improvements in children’s cognitive, motor, and socio-emotional development [1, 8]. Nutrition-sensitive agricultural programmes, when well-implemented, can improve maternal and child dietary outcomes and, in some cases, children’s nutritional status [15, 16]. Further, CT programmes can improve food and nutrition intake, but have more inconsistent effects on micronutrient status and anthropometry [12, 13]. Combining these sectors may lead to substantial gains in effectiveness, efficiency, and cost. Existing evidence highlights the potential for additive and synergistic effects when combining ECD, nutrition, agriculture, and CT interventions [11, 16, 39, 40]. However, there is a need to rigorously assess these potential synergies. This article describes the rationale, design, and methods for the Maziko trial, a cRCT designed to evaluate the impact and cost-effectiveness of an integrated SBC ECD package coupled with nutrition-sensitive SBC and CT on the diets, nutrition, and development of young children and their mothers in rural Malawi. To our knowledge, this is the first study to examine the synergistic effects of combining ECD, nutrition, agriculture, and CT interventions on women’s and children’s diet, nutrition, and development outcomes.

The Maziko study will provide evidence on the effectiveness and cost-effectiveness of integrating ECD, nutrition, agriculture, and CT interventions to support households with young children in rural Malawi. The trial will inform the scaling-up of these services in Malawi. Results are likely to be generalisable to similar rural settings in sub-Saharan Africa with high poverty levels, where households face recurring extreme lean season shocks and constrained financial resources for child diets, nutrition, and development.

## Trial status

Protocol version 4, 12/09/2023. The first participant was enrolled on 2 May 2022 and recruitment was completed on 11 July 2022. Data collection will be completed by June 2025.

## Protocol amendments

Protocol amendments are not planned. If any important protocol modifications are required (such as changes in eligibility criteria, outcome, or analyses), these changes will be reported to the institutional review boards providing ethical clearance for the study. The trial registration will be updated accordingly once approvals are received.

## Dissemination policy

Study findings will be disseminated through in-person workshops with stakeholders in the villages/clusters, districts, and regions where the study is to be conducted; in-person and virtual workshops with key local, national, and international stakeholders; and policy briefs, blog posts, social media posts, peer-reviewed publications, and presentations at scientific and programmatic meetings. All peer-reviewed publications will also be added to the trial registration website.

All authors of peer-reviewed publications must make a substantive contribution to the intellectual content according to the ICMJE authorship criteria. All peer-reviewed publications will contain CRediT (Contributor Roles Taxonomy) author statement or alternative author contribution statement based on journal requirements.

## Data Availability

All members of the Maziko trial team will have access to the final de-identified datasets. Only the PI will retain identifying data on an encrypted password-protected computer for use in tracking and identifying baseline survey respondents during the follow-up surveys. All identifying information will be deleted within 12 months of completing the project. The anonymised data will be made publicly available on the IFPRI website within 12 months of the end of the project. Users of the data will be asked to provide information on how the data are expected to be used to help IFPRI track use of the data for research purposes. Any data required to support the protocol can be supplied on request. The statistical code to replicate findings from individual papers can be made available upon reasonable request to the corresponding author for the paper.

## Abbreviations

ANCOVA: Analysis of covariance
BCC: Behaviour change communication
CAPI: Computer-assisted personal interviewing
CBCCs: Community-based childcare centres
cRCT: Cluster-randomised controlled trial
CT: Cash transfers
ECD: Early childhood development
GoM: Government of Malawi
ICER: Incremental cost-effectiveness ratio
IEYP: Investing in Early Years Program
MDAT: Malawi Development Assessment Tool
MDES: Minimum detectable effect size
MPA: Mean probability of adequacy
NEEP-IE: Nutrition Embedded Evaluation Programme Impact Evaluation
PECD: Protecting Early Childhood Development
RCT: Randomised controlled trial
SBC: Social behaviour change
SCTP: Social Cash Transfer Programme
SoC: Standard of care
